### 203 **4.2 Secondary Efficacy Outcomes**

- 204 1. Proportion of recurrent stroke (ischemic stroke and intracerebral hemorrhage) at 3 months and 12 months
- 205 after randomization;
- 206 2. Proportion of patients with functional independence ( $mRS \leq 2$ ) at 12 months after randomization;
- 207 3. Proportion of patients with no or minimal disability ( $mRS \leq 1$ ) at 3 months and 12 months after
- 208 randomization;
- 209 4. Change in NIHSS score at 3 months after randomization;
- 210 5. Proportion of composite cerebrovascular events (ischemic stroke, intracerebral hemorrhage, myocardial
- 211 infarction, and vascular death) at 3 months and 12 months after randomization;
- 212 6. Difference of EuroQoL Group 5-Dimension (EQ-5D) score at 3 months and 12 months after
- 213 randomization;
- 214 7. Change in Barthel Index (BI) score at 3 months and 12 months after randomization;
- 215 8. Difference of platelet counts and coagulation indicators (prothrombin time, and activated partial
- 216 thromboplastin time) at 3 months after randomization.

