| 3  | Visual fields:
Visual fields (upper and lower quadrants) are tested using finger counting or visual threat, as appropriate. Patients may be encouraged, but if they look at the side of the moving fingers appropriately, this can be scored as normal. If there is unilateral blindness or enucleation, visual fields in the remaining eye are scored. Score 1 only if a clear-cut asymmetry, including quadrantanopia, is found. If patient is blind from any cause, score 3. Double simultaneous stimulation is performed at this point. If the patient is dying, score a 1, and the results are used to respond to item 11. | 0 = No visual loss
1 = Partial hemianopia
2 = Complete hemianopia
3 = Bilateral hemianopia (blind including cortical blindness)                                                                                                                                                                                                                                                                                                                          |
| 4  | Facial palsy:
Ask — or use pantomime to encourage — the patient to show teeth or raise eyebrows and close eyes. Score symmetry of grimace in response to noxious stimuli in the poorly responsive or non-comprehending patient. If facial trauma/bandages, orotracheal tube, tape, or other physical barriers obscure the face, these will be removed to the extent possible.                                                                                                                                                                                                                                                   | 0 = Normal
1 = Minor paralysis (flattened nasolabial fold, asymmetry on smiling)
2 = Partial paralysis (total or near-total paralysis of lower face, central paralysis)
3 = Complete paralysis (of one or both sides, absence of facial movement in the upper and lower face, peripheral paralysis)                                                                                                                                                      |

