| 5a | Left motor arm:
Extend the arm: 90 degrees if sitting or 45 degrees if supine. Drift is scored if the arm falls before 10 seconds. The aphasic patient is encouraged using urgency in the voice and pantomime, but not noxious stimulation. The assessor can lift the patient's arm to the required position and encourage the patient to hold on. Assess the affected side only.                                                                                                                                                                                                                                               | 0 = No drift; limb holds 90 (or 45) degrees for full 10 seconds
1 = Drift; limb holds 90 (or 45) degrees, but drifts down before full 10 seconds; does not hit bed or other support
2 = Some effort against gravity; limb cannot get to or maintain (if cued) 90 (or 45) degrees, drifts down to bed, but has some effort against gravity
3 = No effort against gravity; limb falls
4 = No movement
9 = Amputation or joint fusion, explain: _____ |
| 5b | Right motor arm:
Extend the arm: 90 degrees if sitting or 45 degrees if supine. Drift is scored if the arm falls before 10 seconds. The aphasic patient is encouraged using urgency in the voice and pantomime, but not noxious stimulation. The assessor can lift the patient's arm to the required position and encourage the patient to hold on. Assess the affected side only.                                                                                                                                                                                                                                              | 0 = No drift; limb holds 90 (or 45) degrees for full 10 seconds
1 = Drift; limb holds 90 (or 45) degrees, but drifts down before full 10 seconds; does not hit bed or other support
2 = Some effort against gravity; limb cannot get to or maintain (if cued) 90 (or 45) degrees, drifts down to bed, but has some effort against gravity
3 = No effort against gravity; limb falls
4 = No movement
9 = Amputation or joint fusion, explain: _____ |

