|----|----------------------------------------------------------------------------------------------------------------------------------------------------------------------------------------------------------------------------------------------------------------------------------------------------------------------------------------------------------------------------------------------------------------------------------------------------------------------------------------------------------------------------------------------------------------------------------------------------------------------------------------------------------------------------------------------------------------------------------------------------------------------------------------------------|--------------------------------------------------------------------------------------------------------------------------------------------------------------------------------------------------------------------------------------------------------------------------------------------------------------------------------------------------------------------------------------|
|    | scored if the leg falls before 5 seconds. The aphasic patient is encouraged using urgency in the voice and pantomime, but not noxious stimulation. The assessor can lift the patient's leg to the required position and encourage the patient to hold on. Assess the affected side only.                                                                                                                                                                                                                                                                                                                                                                                                                                                                                                           | 1 = Drift; leg falls by the end of the 5-second period but does not hit bed
2 = Some effort against gravity; leg falls to bed by 5 seconds, but has some effort against gravity
3 = No effort against gravity; leg falls to bed immediately
4 = No movement
9 = Amputation or joint fusion, explain: __                                                                  |

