| 6b | Right motor leg:
Hold the leg at 30 degrees (always tested supine). Drift is scored if the leg falls before 5 seconds. The aphasic patient is encouraged using urgency in the voice and pantomime, but not noxious stimulation. The assessor can lift the patient's leg to the required position and encourage the patient to hold on. Assess the affected side only.                                                                                                                                                                                                                                                                                                                                                                                                                           | 0 = No drift; leg holds 30-degree position for full 5 seconds
1 = Drift; leg falls by the end of the 5-second period but does not hit bed
2 = Some effort against gravity; leg falls to bed by 5 seconds, but has some effort against gravity
3 = No effort against gravity; leg falls to bed immediately
4 = No movement
9 = Amputation or joint fusion, explain: __ |
| 7  | Limb ataxia:
This item is aimed at finding evidence of a unilateral cerebellar lesion. Test with eyes open. In case of visual defect, ensure testing is done in intact visual field. The finger-nose-finger and heel-shin tests are performed on both sides, and ataxia is scored only if present out of proportion to weakness. Ataxia is absent in the patient who cannot understand or is paralyzed. In case of blindness, test by having the patient touch nose from extended arm position. Only in the case of amputation or joint fusion, the examiner will record the score as 9, and clearly write the explanation for this choice.                                                                                                                                                     | 0 = Absent
1 = Present in one limb
2 = Present in two or more limbs                                                                                                                                                                                                                                                                                                            |

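### The NIHSS form in Appendix 3 contradicts itself on visual extinction (item 3), on the code 9 (item 7) and on which limbs to score (items 5 and 6)

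*Protocol*

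**What the plan says.** The NIHSS total has two uses in the protocol. Section 3.3, inclusion criterion 4, admits patients scoring 4 to 15. Section 4.2 lists as its fourth secondary efficacy outcome "Change in NIHSS score at 3 months after randomization". Section 6.1 schedules the scale at randomization, month 1 and month 3. Appendix 3 is the scoring form.

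- **Limb items (5a, 5b, 6a, 6b).** Left and right arm and left and right leg each have their own 0 to 4 score. Each of the four instructions ends "encourage the patient to hold on. Assess the affected side only".
- **Visual fields (item 3).** The item reserves a score of 1 for a definite asymmetry. It then introduces double simultaneous stimulation and adds: "If the patient is dying, score a 1, and the results are used to respond to item 11".
- **Limb ataxia (item 7).** The instruction reads "Only in the case of amputation or joint fusion, the examiner will record the score as 9", but the score column offers only 0, 1 and 2. The limb items, by contrast, print the code in their score columns: "9 = Amputation or joint fusion, explain". Item 10 does likewise for physical barriers to speech.

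The introduction to Appendix 3 requires scores to show what the patient actually does, and an explanation for any item not assessed. It does not say how such items enter the total.

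**The concern.** A rater works from this form at the bedside, and eligibility is settled from it on Day 1. If a rule contradicts the item it belongs to, two careful raters can give the same patient different totals. Near either entry bound that can change who is randomized. Later it adds error to the change score at month 3.

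The limb rule matters most. Whether the second arm and leg are examined depends on how a rater understands the affected side. The form itself foresees deficits on both sides: item 8 has scoring rules for brainstem stroke with loss on both sides and for quadriplegia. Appendix 1 includes vertebrobasilar symptoms among its diagnostic features. Recurrent stroke is itself a secondary outcome, recorded at the same month 1 and month 3 visits, and the form does not say what the affected side is once a second stroke has struck the other hemisphere.

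**Working it through.** The protocol states no NIHSS total or maximum to reproduce, so the check uses the item ranges printed in Appendix 3 and compares the rules with each other.

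**1. Range of the form.** Item maxima, leaving out 9:

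- 1a, 1b, 1c: 3 + 2 + 2 = 7
- 2, 3, 4: 2 + 3 + 3 = 8
- 5a, 5b, 6a, 6b: 4 × 4 = 16
- 7, 8: 2 + 2 = 4
- 9, 10, 11: 3 + 2 + 2 = 7

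Total: 7 + 8 + 16 + 4 + 7 = 42.

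**2. Limb rule.** If only one side is ever scored, one arm item and one leg item drop out: 4 + 4 = 8 points, and the largest attainable total falls to 42 − 8 = 34.

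- Deficit on one side only: the other side would score 0, so the total does not change.
- Deficit on both sides, or new weakness on the other side at follow-up: the total is too low by the other side's score, from 1 up to 8 points, if the rule is read as the index side only and the untested side counts as 0.

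Eight points compares with an entry window of 4 to 15. The rule also fits poorly with its neighbours: separate left and right lines exist so that both can be scored, item 7 has both sides tested, and item 8 provides for loss on both sides.

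**3. Item 3.** Its sentences run in this order: a 1 requires definite asymmetry; double simultaneous stimulation is done; a dying patient scores 1; the result is carried to item 11. Item 11 scores inattention and extinction to stimulation of both sides at once. Dying has no link to the sentence before it, to item 11, or to the item's own condition for a 1. Extinction links to the stimulation step and to item 11, so the structure indicates that extinction was meant. As written, a dying patient without a field defect gains 1 point, and a patient with visual extinction but full fields gets no point on item 3. Either way the total moves by at most 1, which matters for entry only at the edge of the window, such as 3 against 4.

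**4. Item 7.** The instruction requires a value that the score list does not contain. Items 5a to 6b and 10, which use the same code, all list it. Item 7 is the exception.

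**The case against.** The strongest reply concerns the limb rule. The sentence stands under both the left and the right items, so a patient weak on both sides can be said to have two affected sides, and a patient with a new stroke has a newly affected one. Together with the instruction to score what the patient does, a sensible rater might miss nothing. That stands as a possible reading, so an understated total is not demonstrated. It does not remove the fault: the form leaves the choice to the rater, and no later analysis rule can recover a limb that was never examined.

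A reader might go further and infer that the 9s are added into the total. One summed 9 would turn other items adding to 0–3 into 9–12 (wrongly inside 4 to 15), leave 4–6 inside at 13–15, and turn 7–15 into 16–24 (wrongly outside). The protocol does not instruct this. A 9 with an explanation, after grades that stop at 4 or 2, reads as a not-testable code, and its handling may sit in the CRF guidance promised in section 12.2. Limb amputation and joint fusion are also lasting, so a 9 at both visits would cancel in the change score.

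A reader might also infer that extinction is lost altogether. It is not: item 11 still scores it. Finally, section 9.3 requires sites to pass training before starting. That may help, although it does not name the NIHSS and does not correct the printed form.

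**Conclusion.** The point holds as a set of internal contradictions in Appendix 3. Items 3 and 7 are wrong as written. The limb rule is ambiguous and conflicts with the form's layout. The size is at most 1 point for item 3 and none for one-sided deficits under the limb rule. It reaches 8 points only for patients with weakness on both sides or new weakness on the other side, and only if raters take the affected side to be that of the index stroke.

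The documents do not support a claim that totals are known to be wrong for a countable group. A count would need the recurrence rate, the share on the opposite side, the share of those with limb weakness, the frequency of untestable limbs and the raters' reading of the rule. The protocol gives none of these, and the number is probably small. The reach is limited to one entry criterion and one of eight secondary efficacy outcomes. The primary outcome is the mRS and is unaffected. The same form serves both blinded arms, so no bias between them is shown.

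**What to change.** In Appendix 3 and the matching CRF page:

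- **Item 3:** replace the condition that the patient is dying with *extinction is present*.
- **Items 5a, 5b, 6a, 6b:** delete the affected-side sentence and score all four limbs at each visit where the NIHSS is done.
- **Item 7:** add 9 to the score list.
- **As a clarification:** label 9 wherever it appears as a not-testable code kept out of the total.

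The cost is a reissued form, one check of the CRF total and a short training note. Examining the second arm and leg adds little time, and no visits or patients are added. The sample size is untouched.

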**YOUR HEALTH TODAY**

**The questionnaire is completed by:**

- ☐ 1 Patient
- ☐ 2 Patient with the assistance of a third person
- ☐ 3 Proxy (patient's family member)

[figure not shown]

956 **Appendix 5. Barthel Index**

| Item                                      | Scoring criteria                                                                                                                                                                                                                                                                                                 |
|-------------------------------------------|------------------------------------------------------------------------------------------------------------------------------------------------------------------------------------------------------------------------------------------------------------------------------------------------------------------|
| Feeding                                   |  0 Dependent
 5 Needs some help
 10 Independent                                                                                                                                                                                    |
| Bathing                                   |  0 Dependent
 5 Independent                                                                                                                                                                                                                                   |
| Grooming (face, hair, teeth, shaving)     |  0 Needs help
 5 Independent                                                                                                                                                                                                                                  |
| Dressing (buttons, zips, laces)           |  0 Dependent
 5 Needs some help
 10 Independent                                                                                                                                                                                    |
| Bowels                                    |  0 Incontinent or needs to be given enemas
 5 Occasional accident
 10 Continent                                                                                                                                                    |
| Bladder                                   |  0 Incontinent or catheterized and unable to manage alone
 5 Occasional accident
 10 Continent                                                                                                                                     |
| Toilet use (on and off, dressing, wiping) |  0 Dependent
 5 Needs some help
 10 Independent                                                                                                                                                                                    |
| Transfers (bed to chair and back)         |  0 Unable, no sitting balance
 5 Major help (2 people, physical), can sit
 10 Minor help (1 person, verbal or physical)
 15 Independent                                                                 |
| Mobility (on level surfaces)              |  0 Immobile or < 45 meters
 5 Wheelchair independent, including corners, > 45 meters
 10 Walks with help of 1 person (verbal or physical) > 45 meters
 15 Independent (but may use any aid) > 45 meters |
| Stairs                                    |  0 Unable
 5 Needs help (physical, verbal, carrying aid)
 10 Independent                                                                                                                                                           |

957
